### Recruitment

Participant selection will be recruitment based related to clearly defined inclusion and exclusion criteria described before. Selected participants will be required to sign an informed consent form. Project staff will be required to fill data collection forms and study questionnaires that include participant demographic information about age, education, language preference, and a brief medical history. Participant recruitment follows a serial process, as shown in Figure 3.

**Figure 3 figure3:**
[figure not shown]
Flowchart of participant recruitment and study enrollment.

*Community-based recruitment*: Participants will be recruited by community health workers stationed at a mobile testing unit using regulatory body–approved study-designed recruitment materials. Additional recruitment methods will be used, such as outreach activities within the community and appearance at community events and local malls.

*Word-of-mouth recruitment*: Participants will be encouraged to tell others about the study. Once potential participants have been identified through the recruitment modes, they will be approached and informed about the study and the role they will play in the study procedure. The objectives, rationale, eligibility requirements, and procedures of the study will be explained to the participants and will highlight that participation is purely voluntary. The risks and benefits of participation in the study and the rights of participants in the study will also be discussed. The participants will be encouraged to ask questions to ascertain their level of understanding and asked to take flyers home with them to inform other potential participants. Potential participants who meet inclusion criteria will be scheduled and directed to the testing site.

### Enrollment Questionnaire: Inclusion/Exclusion Checklist

An enrollment questionnaire will be administered to establish successful qualification for enrollment. The questionnaire will clearly outline the inclusion and exclusion criteria. If participants satisfy all the inclusion criteria and none of the exclusion criteria, eligibility for enrollment will be confirmed. Enrollment questionnaires will be available in English and will capture information such as participant identification, name and surname, date of birth, nationality, employment status, and recruitment site. Information such as participant initials, date of birth, gender, date of enrollment, and reason for exclusion will be captured on an enrollment log. Once a participant has qualified for enrollment and has signed the informed consent form, the participant will be assigned a unique identification number. Volunteers who do not satisfy inclusion criteria will be documented and reported as exclusions. Further, the reason for enrollment failure will also be recorded.

### Selection and Withdrawal of Study Participants

Participants may voluntarily withdraw participation at any time. In this case, the principal investigator (PI) will acquire all study-related information and the reason for withdrawal will be documented. The information and data collected prior to participant withdrawal from the study may be used for research by the PI or sponsor. This information may be used without identifying any personal information as agreed upon in the informed consent form unless the participant provides a written request prohibiting/limiting the use of their study data.

The PI may decide to limit or withdraw participation of any participant at any point in the study. Further, the sponsor may close the study prematurely for any reasons, including administrative decisions.

### Informed Consent

Prior to any research processes taking place, potential participants will be provided with information about the study, enabling an informed decision regarding further participation. If the participant voluntarily accepts participation, a regulatory body–approved informed consent form will be administered. The form will contain general information about the study and specific information regarding sample collection and all other study procedures.

Potential participants will be encouraged to ask questions to ensure the entire process is clearly understood. Prospective participants will also be informed that they may reject the specimen collection procedure and withdraw from the study at any time. Participants must agree to and submit their informed consent forms (along with demographic data; see below) prior to formal enrollment in the study.

Informed consent will be offered after verbal explanation of the study procedures in English by designated staff. If a participant is found to be unable to read or write, no further consent procedures will be undertaken.

### Demographic and Health Data Collection

All enrolled participants will have the following demographic data captured:

InitialsDate of birthAgeGenderNationality

The participant background information captured will include:

Employment status (employed/unemployed)Years of schooling and level (≤grade 7 primary schooling level/≥grade 8 primary schooling to ≤matric level/≥Technikon, university, and university plus)Reading/writing impairmentLanguage preferenceHIV status (if known)Approximate date of last HIV test

Participants may choose to report their medical health history, which will be documented and archived for statistical review. Information will include:

Self-reported HIV status:Unknown status/never been testedNegative statusSelf-reported medical conditions:DiabetesHypertensionVisual impairmentPregnancyOther

### Testing Procedures

#### Subject Tool Evaluation

After the consenting procedures, enrollment questionnaire, and demographic data have been collected, each participant will be invited into a private area (tent, gazebo setting) and introduced to the clinical staff (nurse/counselor), who will describe the study process. The digital tool interaction is to be completed under the direct observation of the study staff. The nurse/counselor will verbally guide the participant as follows: “This is the part of the study in which you will be asked to use the study product. With this product, you can begin to answer the questions yourself. I will be available to answer any questions or explain further if you require assistance, but would prefer that you try and use the tool on your own. When you are finished, you can let me know and we will proceed to testing.”

Each participant will be presented with a tablet that has the application installed and will be requested to complete the set of questions listed below:

Please select your gender.MaleFemaleTransgenderDate of birth:Please select your race.BlackWhiteIndianColoredOther (please specify)What is your education level?Primary schoolHigh schoolDiploma or certificateTertiaryNone of the aboveWhat is your occupation type?Informal (different employers, depending on job)
How long working away from home (remote)?
1 week per month
2 weeks per month
3 weeks per month
1 month or longer
Working in the same city/area where you live (local)
Formal (permanently employed and same boss)
How long working away from home (remote)?
1 week per month
2 weeks per month
3 weeks per month
1 month or longer
Working in the same city/area where you live (local)
Unemployed (no job)When was the last time you tested for HIV?0-3 months3-12 monthsMore than 12 monthsNever testedDo you use a condom during sex?YesNoSometimesI have never had sex.Please select the gender and age of all sexual partners with whom you had sex in the past 3 months.Number of partners and age groups (Figure 4)No sex in the past 3 monthsWhich of the following sexual activities have you performed in the past 6 months?Anal receptive (you receive penis in anus)Anal insertive (you insert penis in partner’s anus)Vaginal receptive (you receive penis in vagina)Vaginal insertive (you insert penis in partner’s vagina)Oral receptive (your partner sucks your vagina/penis)Oral insertive (you suck partner’s vagina/penis)None of the aboveHave you gone through any of the following in the past 6 months?Sexually abusedStabbedBittenScratchedNone of the aboveHave you experienced/noticed any or many of the following?Weight loss of more than 5 kg over 3 monthsPersistent cold and flu in the past 6 monthsPersistent diarrhea and fatigue in the past 6 monthsRecurring night sweats in the past few monthsWhite patches in mouthBad breathSore throatUlcersDifficulty in eatingDry coughWet cough for more than 3 weeks in the past 1 yearBlood in cough in the past 1 yearPersistent fever or chills for no known reasons in the past 1 yearPersistent shortness of breath or chest pain in the past 1 yearHave you experienced/noticed any or many of the following?Genital warts (small bumps on genitals)Genital herpes (genital pains or sore genitals and open sores on genitals)Gonorrhea (bacterial infection: white or yellow liquid visible in genital region)Syphilis (rash on the body or painless sore on genitals, rectum, or mouth)Gonococcal (painful urination and abnormal discharge from penis or vagina)None of the above

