A risk assessment tool is a set of simple and easy*-*to*-*understand questions *that* are answered by the participant(s)*,* and based on the responses, a risk probability is calculated. The questions are related to demographics, sexual behavior, sexual history, personal behavior, lifestyle*,* and medical history. The questions are scientifically designed based on the HIV correlation data from published research and clinical trials. The tool makes use of scientific algorithms to determine the risk probability and *provides* the outcome as low risk*,* medium risk*,* or high risk. Diagnostic assistive assessment is performed on a mobile device by the patients themselves*,* thus eliminating external influences and hence providing more accurate information.

In 2019-2020, a feasibility study was conducted with over 1000 participants at the Wits Reproductive Health and HIV Institute’s (WRHI) HIV self-testing assessment and research (HSTAR) Africa site in Johannesburg, South Africa. This study sought to understand the correlation between HIV status and factors such as demographics, sexual behavior and history, personal behavior and lifestyle, and symptoms, individually.

Analysis of the data collected from this feasibility study showed correlations between HIV status and all the variables. The main inference made was that patients can be grouped based on multiple factors as follows:

Primary features (demographics)Secondary features (lifestyle)Tertiary features (sexual behavior)Auxiliary features (symptoms)

Examples of the detailed analysis are shown in Figure 1.

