### Design

In this longitudinal, supervised learning study, the data collected will be split into a training set and a validation set and the data used to validate the model will not be used in the training of the model, which will eliminate the need for a control group. This study will build on the feasibility study described before. The major variable shift is from a clinic-based setting to an in-field setting, which includes rural and semirural sites.

During the evaluation, the untrained user will be assessed thoroughly for process success or difficulty by a silent, non-interacting nurse/counselor. Overall, the process will include (1) completing a series of behavioral questions on an application system without the assistance of trained staff (assistance will only be provided on user request); (2) HIV testing being performed by the trained nurse/counselor (for comparator data to the risk assessment scores); and (3) communicating test results and completing a survey questionnaire developed to collect data on user experience.

All participants will have two rapid HIV tests performed. In the event of a positive HIV diagnosis, the participant will be referred for clinical treatment and care. If a participant tests negative, they will be found eligible for visit 2, which will occur 3 months after visit 1. At visit 2, the participant will follow the same process as that completed at visit 1 (Figure 2).

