### Blinding of Results

This will be a blinded study. Participants will not be aware of their risk assessment scores. There will be no randomization of participants, as all participants will be required to interact with the machine-guided tool. This study will make use of supervised learning in which the data set will be collected and then used to train and test the machine learning model that has been created. The data will be collected in a specific area, and selection will be random. The data, however, will be split into training and validation data using a randomized split algorithm commonly found in statistical and data processing languages such as R and Python.

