#### Error and Failure Rates

Critical errors occur when participants make operational errors during interaction with the machine-guided tool. Project staff will aid participants, if needed, to ensure accurate completion of all behavioral questions that contribute directly to risk assessment scores.

The failure rate (cases where the risk score is high and the test result remains negative for both visits) will be identified and reported as the number or a percentage of failed cases of the total number of cases completed in the study.

It should be noted that failure due to critical errors (participants not being able to successfully complete the digital assessment) will not be included in the analysis.

The type of behavioral questions and the weighted score for each will be monitored and evaluated for continuous improvement and refinement purposes.

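### Answers said to be free of external influence are given under staff observation and with staff help, and the blinding clause does not cover whoever reads the reference HIV test

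*Protocol article*

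**What the plan says.** All references are to the protocol article.

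- **Introduction.** Patients carry out the assessment themselves on a mobile device, "thus eliminating external influences and hence providing more accurate information".
- **Subject Tool Evaluation.** "The digital tool interaction is to be completed under the direct observation of the study staff". The nurse/counselor's script adds "I will be available to answer any questions or explain further if you require assistance" and ends "When you are finished, you can let me know and we will proceed to testing". The questions that follow cover condom use, number and age of partners, anal sex, sexual abuse and sexually transmitted infections.
- **Design.** "the untrained user will be assessed thoroughly for process success or difficulty by a silent, non-interacting nurse/counselor". The same section has "HIV testing being performed by the trained nurse/counselor (for comparator data to the risk assessment scores").
- **Error and Failure Rates.** "Project staff will aid participants, if needed, to ensure accurate completion of all behavioral questions that contribute directly to risk assessment scores".
- **Blinding of Results.** "This will be a blinded study. Participants will not be aware of their risk assessment scores". No other person is named as masked.
- **Data Analysis.** The endpoint is the agreement between the risk score and the confirmatory test result. The Abstract treats the test result as the ground truth.
- **Confirmatory Procedures.** Two rapid tests must agree. A discordant pair, in either direction, is indeterminate and is repeated.
- **Secondary Objectives.** Usability is measured by observation, with a staff checklist of success and of completion of the questions.

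**The concern.** Two separate risks follow, one for the predictor and one for the reference standard.

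**Predictor.** The behavioral answers are the model's inputs. People asked about stigmatized behavior in front of a counselor may under-report it. The training and validation sets are a random split of data collected in the same way, so both halves would carry the same distortion and internal validation could not reveal it. The accuracy obtained would describe observed use with help at hand. The Discussion, by contrast, promotes the tool for its privacy and for sparing people a clinic visit.

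**Reference standard.** For an endpoint that compares a score with a test result, the masking that matters most is that of the person reading the test. Masking participants to their own score does not provide it. If a reader who knows the answers or the score handles a faint line or a repeat differently, agreement between score and test could be inflated.

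**Working it through.** No figure in the document bears on this point, so there is nothing to recompute. The check sets the sections side by side.

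**1. Is external influence eliminated?** The Introduction says so without qualification. Subject Tool Evaluation requires direct observation, and Secondary Objectives confirms observation as the way usability is measured. An observed session does not meet the Introduction's description, even though the participant enters the answers personally.

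**2. What does the observer do?** Three descriptions are given:

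| Section | Role of staff during completion |
|---|---|
| Design | Silent and non-interacting, with help on the user's request |
| Subject Tool Evaluation | Present, offering to answer questions and explain |
| Error and Failure Rates | Aiding if needed, so that the scored questions are completed accurately |

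The first two can be brought close together by reading silence as the default and help as the exception. The third goes further. Its trigger is need rather than request, and its aim is the accuracy of the very answers that produce the score. A non-interacting observer cannot provide that.

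**3. Who performs the reference test?** Design assigns both observation and HIV testing to the nurse/counselor. The script moves from completing the tool straight to testing, and Testing Procedures then has a trained nurse/counselor perform the two tests and communicate the results. The role is the same. That the individual is the same is a reasonable inference but is not stated.

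**4. Who is masked?** Only participants, and only to the score. No section says that the person performing or reading the tests is kept from the answers or the score. No section says that this person sees them either.

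**5. Does it recur?** Yes. Design has visit 2 follow the same process as visit 1, so both analyses are exposed.

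**6. Can either bias be sized?** No. The document gives no rate of under-reporting with and without an observer, no rate of discordant or equivocal rapid tests, and no information on what staff can see on the tablet.

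**The case against.** **Observation has a declared purpose.** The secondary objectives include difficulty in using the tool and comprehension of specific questions. This stands as a reason to observe and as a real cost of hiding the screen. It does not support the claim that external influence is eliminated. The checklist described under Secondary Objectives records success and completion, neither of which requires reading individual answers.

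**The Introduction describes the tool in general.** It says that patients do the assessment themselves, not that they are alone. In this study they enter their own answers in a private area and are encouraged to work unaided. This is fair, and it would be wrong to describe the session as an interview. The unqualified statement still does not describe the conditions under which this study's data arise.

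**The reference test has its own safeguard.** Two rapid tests must agree, discordant pairs are repeated, and the rule makes no reference to the score. This limits reader bias and makes the blinding part the weaker of the two, but it does not replace masking of the reader.

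**A score may not exist at the time of testing.** Blinding of Results has data collected and then used to train the model, and six algorithms are still to be compared. Other parts describe a tool that computes a score from the answers, and the blinding clause presupposes one. The document is ambiguous here. The answers exist at that moment in any case.

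**Seating is an operational detail.** A condensed article may leave it to procedures not shown, so its absence is not the fault. The fault lies in what is printed: conflicting descriptions of staff involvement, and a claim of blinding that reaches only participants.

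A reader might infer that one nurse watches the answers and then reads the test knowing the score, so that the reference result is contaminated. The document does not establish this: it states neither that one individual does both nor that staff see the answers or the score. A reader might also multiply an assumed denial rate into an item's sensitivity and call the result the tool's loss. That is not supported, because the score combines demographic, lifestyle, sexual-behavior and symptom features in a model fitted to answers given under the same conditions.

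**Conclusion.** The concern holds as an inconsistency in the text and an avoidable weakness in the design, not as demonstrated bias. The Introduction's claim is incompatible with the observed and assisted completion in the procedures, and the Design section's description of the observer does not fit the help described under Error and Failure Rates. The declared blinding omits the person whose masking matters most for the agreement endpoint.

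The size of either effect cannot be derived from the document. Under-reporting would weaken or distort the behavioral predictors, while biased reading would raise agreement; the two need not cancel, and no net direction can be given. The conclusion on the test reader assumes only that the printed blinding clause is complete. If the full protocol masks that person, this part is met by saying so. The change is worth making because it costs little.

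**What to change.** 1. Seat the observer where the participant, but not the screen, can be seen, approaching only on request. Let the application log completion.
2. Extend the blinding clause: whoever performs and reads the rapid tests does not see the answers or the score until the results are recorded. State whether the observer and the tester are the same individual and whether staff can see the score.
3. Reconcile Design, Subject Tool Evaluation, and Error and Failure Rates on when and how staff may help.
4. Qualify the Introduction's statement on external influence, and report accuracy as measured under observed use.

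**Cost.** A seating instruction, an application setting and a few sentences, with no extra staff. The downside is somewhat less information on which question caused difficulty, which bears on the usability and comprehension objectives. Noting each request for help on the checklist would recover part of it.

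**If it is too late.** The Results section says data collection has commenced. If it is too far advanced for steps 1 and 2, correct the wording, state who was in fact masked and to what, and report observed completion as a limitation.

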#### Interaction Between Variables

A bivariate analysis will be performed for each variable to investigate the relationship between the respective variable and HIV status. This will then further be used in feature engineering.

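### For acts on a penis, the oral-sex options use 'receptive' and 'insertive' the opposite way round from the anal and vaginal options in the same question, so the two oral variables can be answered inconsistently or read as the opposite exposure

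*Protocol article*

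**What the plan says.** Under Subject Tool Evaluation, the Protocol article prints the items that the participant completes on a tablet. One item asks about sexual activities in the past 6 months and offers six acts plus a none-of-the-above choice. Each act has a role label followed by a bracketed plain description.

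- Anal: "Anal receptive (you receive penis in anus)Anal insertive (you insert penis in partner’s anus"
- Vaginal: "Vaginal receptive (you receive penis in vagina)Vaginal insertive (you insert penis in partner’s vagina"
- Oral: "Oral receptive (your partner sucks your vagina/penis)Oral insertive (you suck partner’s vagina/penis"

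The article gives no separate definition of the oral roles.

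Three other places bear on how the answers are used. The Introduction says of the tool: "The questions are scientifically designed based on the HIV correlation data from published research and clinical trials". Error and Failure Rates says: "The type of behavioral questions and the weighted score for each will be monitored and evaluated for continuous improvement and refinement purposes". Interaction Between Variables says: "A bivariate analysis will be performed for each variable to investigate the relationship between the respective variable and HIV status", and adds that the result goes into feature engineering.

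**The concern.** Four of the six options fix what the role words mean: receptive is the person whose body takes the penis, insertive the person whose penis enters the partner. The last two options appear to turn this round without saying so.

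Two things are at stake.

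- **Data quality.** A participant who carries the meaning over from the four options above and answers from the label will tick the opposite box from one who reads the bracket. The recorded variable would then mix two exposures.
- **Interpretation.** Whoever later reads a table row or feature called oral receptive will naturally give it the anal and vaginal meaning, and so attribute the finding to the other partner.

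The described checks are not aimed at this. The forced completion under Missing Data prevents blanks, not wrong answers. The staff checklist under Secondary Objectives records whether the tool was used successfully and the questions completed, not whether an option was understood as intended. Correct comprehension of specific behavioral questions is itself one of the study's secondary objectives, so contradictory wording bears on a stated objective.

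**Working it through.** The article states no figure to reproduce. The check is to take the rule set by the anal and vaginal options and apply it to the oral ones.

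**Rule from the anal and vaginal options.** Receptive: the respondent's body receives the partner's penis. Insertive: the respondent's penis enters the partner. The four labels agree with each other under this rule (4 of 4).

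**The rule applied to the oral options.**

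| Bracketed act | What happens | Role under the rule | Printed label |
|---|---|---|---|
| Partner's mouth on respondent's penis | Respondent's penis enters partner | Insertive | Receptive |
| Respondent's mouth on partner's penis | Respondent's body receives penis | Receptive | Insertive |
| Partner's mouth on respondent's vagina | No penis involved | Not defined | Receptive |
| Respondent's mouth on partner's vagina | No penis involved | Not defined | Insertive |

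For acts on a penis, both oral labels (2 of 2) are opposite to the rule. For acts on a vagina, the rule assigns no role.

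**Two simple records, answered by the brackets.** A man who only ever inserts his penis is recorded as vaginal insertive and oral receptive. A woman who only ever receives a penis is recorded as vaginal receptive and oral insertive. Each has one role throughout but carries both role words.

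**Where the label could do harm, and what the article shows.**

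1. *A combined receptive or insertive feature across anal, vaginal and oral acts.* This would add opposite exposures together. The article mentions feature engineering but describes no such pooling.
2. *A role-specific weight matched to the option by its label.* This would attach to the wrong partner for acts on a penis. The article says that questions are weighted and were designed from published correlation data. It gives no weight for the oral options.
3. *A bivariate result reported under the label.* This analysis is planned for every variable. The estimate would be correct for the bracketed act if participants answered by the bracket, but the label invites the opposite reading.
4. *A model with one input per option* (the six algorithms under Machine Learning Algorithm, fed the options separately). Renaming a column changes neither the fit, nor the predictions, nor the confusion matrix. Only mixed answering could affect it.

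**The case against.** The best defence is that the oral labels follow everyday speech, in which a person receives oral sex. That probably explains the wording, but the same word still has two opposite meanings within one checklist, with nothing to mark the switch.

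The second defence is that every option carries a concrete description, participants must be able to read English, and staff are available to explain and to help secure accurate completion. This makes answering from the label less likely and stands as mitigation. It does not correct the label, and help comes mainly on request, which a participant who is confidently wrong will not make.

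The third defence is that no analysis described in the article uses the role. This stands, and it limits the point. A reader might infer that the risk score has oral exposure reversed, or that everyone who reports oral acts on a penis in one direction is misclassified. The article supports neither. It shows no pooling and no role-specific oral weight, and a participant who answers by the bracket is recorded correctly for the act described.

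A reader might also want to quantify the dilution. If a fraction m of those reporting only one direction answered in reverse, equally in both HIV groups, the difference between groups among them would be multiplied by 1 − 2m. But the article gives no basis for any value of m, and the factor does not apply to people who report both acts or neither. It yields no error rate for this study.

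**Conclusion.** The point holds as a contradiction in the wording of the study instrument. Two of six options use the role words against the meaning set by the other four for acts on a penis, and without a defined meaning for acts on a vagina. What follows is a risk of mixed answering and a clear risk that results are read as the opposite exposure. A reversed risk score is possible but not shown, and no numerical effect on performance can be claimed. The conclusion rests on the options as printed and on the assumption that the analysis would carry the printed labels forward as variable names. It should be corrected because the item is self-completed, feeds a planned analysis of every variable, and costs almost nothing to put right.

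**What to change.** **In the analysis.** Name and report the two oral variables by the act in the bracket: partner's mouth on the respondent's genitals, and respondent's mouth on the partner's genitals. Keep both out of any combined receptive or insertive feature and out of any weight taken from a role-based source. This works for data already collected and needs two entries in the data dictionary.

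**In the application.** Remove the two role words from the oral options and keep the plain descriptions. Do not simply swap the labels: each oral option covers both penis and vagina, so a swap would leave the vaginal acts with equally undefined role words.

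**Cost.** Two on-screen labels and two variable names, with no extra participants or data. There is one small downside. The Results section says that data collection has begun, and the Design section has visit 2 repeat the visit 1 process, so a change now could fall between a participant's two visits. Record the date of the change so that answers before and after it can be compared.
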